**7 Dissemination of result and publication policy**

The results will be published in an international journal for cardiac intervention.

**8 Duration of the project**

It is feasible to include 120 patients in our study within a 12 months period

**9 Problems anticipated**

Stent under expansion and stent fracture in the Absorb group is a potential problem. If technical problems with BVS or stentfracture/damage occurs, implanting DES (Xience) will be used as a “bailout” strategy.

**10 Project management**

The Steering Committee is the main policy and decision-making committee of the study and has final responsibility for the scientific conduct of the study.

The specific tasks of the Steering committee is to (1) approve the study protocol; (2) approve amendments to the protocol; (3) establish the organizational structure; (4) select the members of the various committees; (5) review the activities of the study committees and change these committees if found necessary, (6) act upon recommendations of the DSMB; (7) approve study reports and papers for publication.

The Steering Committee meets at the request of the Principal Investigators and/or the DSMB.

The Steering Committee constitutes: [name], [name], [name], [name], [name] and [name].

**11 Ethics**

**11.1 Ethical conduct of the study**

The study will be conducted in accordance with the protocol, applicable regulatory requirements and the ethical principles of the Declaration of Helsinki as adopted by the 18th World Medical Assembly in Helsinki, Finland in 1964 and subsequent versions.

It is the responsibility of the investigator to obtain approval of the study protocol/protocol amendments, the patient information and the informed consent form from the Ethical Committee for all patients included in the study.

**11.2 Risk, side effects, advantages and disadvantages in participating in the study**

The extra risk for the patient during the index procedure is minimal as the both OCT and the stents used in both arms are considered safe. The primary procedure time will be about 10-20 minutes longer.The BVS has lower structural strength, but has the advantage of leaving behind now foreign object in the body after resorbtion.

The extra risk is primarily related to the control angiography. Major adverse effects are related to bleeding and hematoma at access point. More serious events such as cerebral insult and damage of coronary vessels are very rare (< 0, 5%), but a potential risk for the patient. The radiation required for a single angiogrammay cause a small increase in risk of developing cancer from 25,00% to 25.01%.

OCT does require an infusion of about 15-20 ml of contrast medium. This is a small dose, and should not pose any threat of contrast induced nephropathy for the individual with a GFR > 45. The risk is < 0,1%. Wire manipulation gives some risk for wire induced damage to the vessel, e.g. dissection and perforation, but is rare < 1%. With FD OCT patients in a minority of cases experience transient chest pain oppression during acquisition. T wave abnormalities have been observed (10%), but no major vascular complications (1).

The follow up by phone and one clinical visit cause some inconvenience for the participants.

Given the potentially benefit of the study, the risks involved are small and can be ethically justified.

**11.3 Patient information and consent**

The study group has opted for an initial oral consent before inclusion. In a setting of an acute STEMI, a delay in the revascularization of an occluded vessel will cause further myocardial damage. It will also not be clear if the patient is eligible for the study until an angiography has been done and flow in the vessel has been established.

Acquiring a written consent during the procedure will be impossible, as most procedures are done with access through the right wrist.

Acquiring written consent post procedure allows the investigator the time to fully explain the study in detail and sufficient time for the participant for consideration. A third party may also be present or consulted if preferred.

In our opinion, this is acceptable, because the primary risk and inconvenience is during follow up. The participants can withdraw their consent at any stage, including not going through with follow up angio.

**11.4 Withdrawal**

A participant will be considered withdrawn from the study if judged by the investigator as:

Not eligible

Protocol violation

Participants decides to withdraw consent

If participant withdraws consent, data collected up until withdrawal will be kept in the study if participant agrees.

Participants who does not return for follow-up will be described as “lost to follow up”.

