**2.0 Study design**

The study is a prospective, randomized, controlled, non-blinded, multicenter study comparing metallic drug eluting stent with bioresorbable scaffold in STEMI patients. Primary endpoint Coronary Stent Healing Index, see 2.2.6 for definition.

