**2.3 Treatment step-by-step**

Before arrival et cath lab, loading with acetylic salisylic acid and one of the antiplatelet agents clopigrogel/pragusgrel/ticagrelor is mandatory. Heparin or bivalirudin at start of procedure. After angiography and confirmation of presence of thrombus GpIIb/IIIa inhibitors are administered at operators discretion.

After thrombus aspiration with TIMI flow 2 or more the patient will be asked to participate in the study. Oral consent witnessed by staff non-affiliated with the study will be obtained.

OCT scan will be performed after 0.2 mg intracoronary nitroglycerine for sizing and lesion evaluation. The patient is then randomized into one of two arms in a 1:1 distribution:

1. Direct stenting with everolimus eluting stent
2. Direct stenting with bioresorbable stent

Direct stenting is the preferred method of implantation to keep procedure as short and simple as possible. Predilatation will not considered protocol violation if deemed necessary by operator. After stenting and post dilation at operator’s discretion, a second OCT will be performed. Any further post dilatation will be performed at operator’s discretion. A final OCT will be done if further postdilatation is performed. 0.2 mg intracoronary nitroglycerine is administered before each OCT scan.

Patient will be asked to sign an informed consent after the procedure (<24 hrs).

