**3.2 Secondary endpoints and other variables**

Differences in categorical variables between the two groups will be analyzed using the chi-square test or Fisher´s exact test. Continuous variables will be analyzed using independent sample t-test and Mann-Whitney U-test, and time to event data will be analyzed using the Kaplan-Meier method and the log-rank test. OCT and angiographic parameters will be evaluated by Spearman correlation analysis. Binary logistic-regression analysis will be performed to identify independent predictors of difference in outcome. Pre and post PCI OCT of vessel size, lesion severity, lesion length. All p-values are two-sided. Level of significance is 5%. The analysis is performed on an intention to treat basis and by actual treatment.

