**3.4 Analysis of the population**

The primary endpoint will be analyzed according to the intention-to-treat principle.

Per protocol analysis of actual treatment will be performed.

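### Section 11.4 lets the investigator, who knows the arm, withdraw patients for ineligibility or protocol violation at any time, and is not reconciled with the intention-to-treat analysis in 3.2 and 3.4

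*Protocol*

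**What the plan says.** Protocol 11.4 states: "A participant will be considered withdrawn from the study if judged by the investigator as", followed by three grounds: not eligible, "Protocol violation", and the participant's own decision to withdraw consent. The first two rest on the investigator's judgement, and no time limit is attached to any of them. The only rule on data is for the third ground: "If participant withdraws consent, data collected up until withdrawal will be kept in the study if participant agrees". Nothing is said about follow-up or data for patients withdrawn on the first two grounds.

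On the analysis, 3.4 states: "The primary endpoint will be analyzed according to the intention-to-treat principle", and then "Per protocol analysis of actual treatment will be performed". Section 3.2 says much the same: "The analysis is performed on an intention to treat basis and by actual treatment".

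On design, 2.0 states: "The study is a prospective, randomized, controlled, non-blinded, multicenter study comparing metallic drug eluting stent with bioresorbable scaffold in STEMI patients". Section 2.3 puts randomisation in the catheterisation laboratory, after oral consent and a first OCT and directly before stenting: "The patient is then randomized into one of two arms in a 1:1 distribution". Section 2.6 places the follow-up angiography and OCT at 12 (± 1) months.

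**The concern.** An intention-to-treat comparison needs every randomised patient to stay in the assigned arm and, as far as possible, to contribute an outcome. Section 11.4 gives someone who knows the arm, and often the acute result, a route by which randomised patients leave the study on a judgement made after randomisation. A patient who leaves before month 12 may have no primary outcome.

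Two things are at stake. First, if violators leave the study, the set analysed under the intention-to-treat label becomes close to a per-protocol set, and the two analyses that 3.4 keeps apart converge. Second, if removal depends on arm and result, the randomised comparison is biased. In a non-inferiority trial of this size a few patients can move the estimate by a noticeable part of the margin.

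**Working it through.** **The text.** The sections set side by side:

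- 11.4: withdrawal follows from the investigator's judgement, on grounds that include protocol violation, at any time.
- 3.2 and 3.4: intention-to-treat, with per-protocol or actual treatment as a further analysis.
- 2.0 and 2.3: open-label; treatment starts straight after randomisation, so a violation in the treatment phase arises after randomisation with the arm known.
- 2.6: the OCT that yields the primary endpoint comes about a year later.

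No sentence keeps patients withdrawn for ineligibility or violation in follow-up or in the intention-to-treat set. Section 2.3 declares predilatation not to be a violation if the operator deems it necessary. Section 9 plans bailout with a metallic stent in the scaffold arm, and section 5 makes it reportable, but neither says whether it counts as a violation.

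**Inputs for an illustration.** Section 3.3 gives planning figures only for minimum flow area (MinFA): mean 4.95 mm², SD 1.39 mm², margin 0.72 mm², alpha 0.05, power 0.85, 54 per group. Section 2.2 gives 120 patients, which is 60 per arm at 1:1. The protocol gives no SD or margin for the Healing Index, so the size can be shown only on MinFA.

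**The plan's own figure.** With true difference 0 and one-sided alpha 0.05:

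n = 2 × (1.645 + 1.036)² × 1.39² / 0.72² = 2 × 7.19 × 1.932 / 0.518 ≈ 53.6, so 54 per group. This matches 3.3. (One-sided 0.025 would give 67.)

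**Loss of power.** 120 − 108 = 12 patients, or 10%, may be lost for all reasons. Power by the noncentral t distribution, one-sided 0.05, is 88.0% at 60 per arm, 86.5% at 57, 84.8% at 54 and 80.9% at 48. The loss of numbers alone is modest.

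**Selective removal.** Assumption, not from the documents: k of 60 scaffold patients are removed, and their mean MinFA lies g below the mean of the whole arm. The mean of those kept rises by k × g / (60 − k). The type I error is taken with the true difference at the margin, SD held at 1.39 and one-sided alpha 0.05.

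| k | g (mm²) | Shift (mm²) | Share of 0.72 | Type I error |
|---|---|---|---|---|
| 3 | 1.39 (1 SD) | 3 × 1.39 / 57 = 0.073 | 10% | about 9% |
| 3 | 2.78 (2 SD) | 3 × 2.78 / 57 = 0.146 | 20% | 14% |
| 6 | 1.39 (1 SD) | 6 × 1.39 / 54 = 0.154 | 21% | about 15% |
| 6 | 2.78 (2 SD) | 6 × 2.78 / 54 = 0.309 | 43% | 32% |

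Removing poor results from the metallic arm would give shifts of the same size the other way.

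**The case against.** The strongest reply is that 11.4 never says follow-up stops or that the patient leaves the analysis. Sections 3.2 and 3.4 state intention-to-treat without exception, 2.6 exempts nobody from the 12-month examination, and a SAP may define how withdrawn patients are counted. This stands in part. A reader might infer a flat contradiction, or that withdrawn patients certainly have no 12-month OCT, and the text supports neither. What remains is that withdrawal from the study ordinarily ends participation, that nothing here says otherwise, and that a SAP cannot recover an OCT that was never acquired.

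Second, ineligibility has a natural and harmless use. Oral consent, aspiration, the flow check and an OCT all precede randomisation (2.3), and 11.3 explains that eligibility is unclear until angiography is done and flow is restored. This stands for that ground, although the wording does not confine it to that window. It does not help with protocol violation.

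Third, a reader might infer that the rule clears out acute scaffold failures and so favours non-inferiority, or that the contraindications in 2.2.4 are the very features that make a scaffold fail. The documents do not support this. Section 2.2.4 applies to both arms. Sections 1, 9 and 11.2 mention lower strength, under-expansion and fracture without linking them to calcification or side branches. Nothing classes an acute scaffold failure as a violation, and violations can occur in either arm.

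Fourth, a larger effect can be produced by assuming that every removed patient had a MinFA near 1.0 mm². That value lies (4.95 − 1.0) / 1.39 = 2.8 SD below the planning mean, and nothing in the protocol supports it for all removed patients.

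**Conclusion.** The point holds as an unreconciled rule. Section 11.4 allows withdrawal after randomisation on the judgement of an investigator who knows the arm, while 3.2 and 3.4 require intention-to-treat. Followed as written, it can cost randomised patients their primary outcome and blur the line between the two analysis sets. The risk of selective removal is real in an open-label non-inferiority trial, but its direction and frequency are not established by the documents.

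The conclusion rests on the text and on no figure. The 10 to 20% of the margin for three removals is an illustration. It assumes that all removals fall in one arm and lie 1 to 2 SD below its mean, and it is on MinFA, not on the Healing Index. The change should be made, and no planned number alters because of it.

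**What to change.** Reconcile 11.4 with 3.4:

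- Limit ineligibility as a ground for withdrawal to the time before randomisation.
- Remove protocol violation as a ground.
- State that ineligibility or a violation found after randomisation is recorded, does not by itself end study participation or data collection, does not remove the patient from the intention-to-treat set of the randomised arm, and is used only to define the per-protocol set.
- State that a missing 12-month OCT is handled as missing data within intention-to-treat. Whether an individual patient undergoes the invasive angiography and OCT remains a clinical and consent matter, and this change does not decide it.

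The cost is a short amendment and a few more patients followed at visits already planned.

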**12 Biological material**

Plasma from blood drawn from aspiration catheter and peripheral vein will be frozen and kept for later analysis for markers of myocardial ischemia and necrosis. Thrombus from aspiration catheter will be fixed in formalin and sent to Amsterdam Medical Center for further analysis.

**13 Study plan**

Launch of study is expected by July 2014. Inclusion of patients is expected to last until1st quarter of 2016. Last follow up is then 1^st^ quarter of 2017.

**14 Economy**

Investigator has received an unrestricted grant from ST Jude Medical to cover cost of OCT core lab.

The individual hospital departments will cover cost of stents, OCT and expenses anticipated with follow up. Department of Heart Disease at Haukeland University Hospital will also have a study- and image- technician available to assist.

Investigator will apply for a Helse Vest PhD grant to cover labor cost of investigator and assisting staff.

The study has potential commercial interest for Abbot Vascular Solutions.

